### Interventions to be measured

#### Surveys

##### Non-validated, sociodemographic survey

We will administer an 11-question survey to collect information about participants’ age group, ethnic background, marital status, employment status, level of education, smartphone and tablet computer ownership, obstetric history, and personal history of depression.

##### Whooley questions

The Whooley questions were developed as a case-finding instrument for depression in primary care.^24^ This two-question instrument assesses depressed mood and anhedonia that have been present during the past month. Respondents are required to answer *Yes* or *No* to each question.

##### Edinburgh Postnatal Depression Scale

The EPDS is a 10-item self-administered survey that was originally developed to screen for postpartum depression.^25^ Since then it has been validated for use in the perinatal period and for use in community and clinical settings. This instrument assesses feelings of guilt, sleep disturbance, anhedonia and suicidal ideation that have been present during the past 7 days. Each question is scored on a 4-point scale ranging from 0 to 3 points. An overall score is generated from the sum of these responses.

Although there is variability in the diagnostic accuracy of different EPDS scores, the following thresholds are commonly used: 10 points for possible depression, 13 for probable depression and 15 for antenatal depression.^26^ In addition, special attention should be paid to item 10, as it deals with suicidal thoughts. Based on these scores, a clinician would be prompted to refer a woman to a mental health professional.

The EPDS is a valid and reliable tool for identifying women who are at risk of depression, both during pregnancy and postpartum. This instrument is also sensitive to changes in the severity of depression over time.^25^ The EPDS can be reproduced without further permission provided that the original source of the scale is cited in each reproduced copy.

##### Non-validated, momentary mood questions

We will administer five momentary questions to assess participants’ mood, sleep, worry, enjoyment and energy (see online supplementary appendix 3). These questions are based on the work of a research fellow at the Collaboration for Leadership and Applied Health Research and Care for the East of England.^27^ Each question will be mapped onto 5-point pictorial scales, ranging from 1 (low) to 5 points (high). For the purpose of this feasibility study, we will not perform any overall score calculation or attempt any validation of these questions.

10.1136/bmjopen-2016-014469.supp3Supplementary appendix 3

##### Non-validated, contextual questions

Two contextual questions will complement the momentary mood questions (see online supplementary appendix 3). They will assess (1) participants’ location and (2) the activity in which they were engaged at the time they were required to complete the five momentary mood questions.

##### Non-validated, poststudy acceptance survey

We will administer 13 questions (to participants completing retrospective assessments) or 14 questions (to participants completing retrospective plus momentary assessments) at the end of the 6-month participation period (see online supplementary appendix 4). The purpose of these questions is to assess the acceptability to participants of BrightSelf in the context of their antenatal care, and to gather information about their experience of using it. These questions were derived from the Usefulness, Satisfaction and Ease of Use (USE) questionnaire^28^ (which focuses on usability) and also include a question concerning the desire to continue use (as used to assess engagement^29^), as well as questions regarding the experience of use and self-report. We will administer them as a web survey through Snap survey software^30^ by sending participants a link via e-mail or short messaging service (SMS).

10.1136/bmjopen-2016-014469.supp4Supplementary appendix 4

##### Mobile system

BrightSelf is a mobile system for the collection of self-reports, both retrospective and momentary, during pregnancy. This system is not a diagnostic tool and is not intended to replace the role of clinicians within antenatal or mental healthcare pathways.

This system elicits retrospective reports through the EPDS, and momentary reports according to the five constructs of mood, sleep, worry, enjoyment and energy. In addition, the system can suggest brief activities that users can perform to lift their mood, additional information about the system and the feasibility study, additional resources should they need immediate help, and a visualisation of past self-reports. We will emphasise to the participants that BrightSelf is not a clinical tool, and that if they feel they need immediate help at any point during the study they should contact their general practitioners.

BrightSelf consists of mobile applications for Android and iOS operating systems, a backend for the storage and management of data, and a website that supports the monitoring of data.

A complete description of BrightSelf is the aim of another publication. Here we describe the two features that are most relevant to this feasibility study, namely the collection of retrospective and momentary self-reports.

##### Check Back

This feature will enable the administration of the EPDS. It consists of two introductory screens informing participants of the retrospective nature of this scale and its intended applications. These screens will be followed by the 10 EPDS questions, presented one question per screen, using radio buttons to capture participants’ responses (figure 1).

**Figure 1 F1:**
[figure not shown]
BrightSelf—Check Back (screenshot).

##### Check In

This feature will enable the administration of the five momentary questions and the two contextual questions. The first five questions will be presented using a 5-point pictorial scale with temporary supporting text (see figure 2 for an example). The last two questions will use radio buttons to capture participants’ responses.

**Figure 2 F2:**
[figure not shown]
BrightSelf—Check In (screenshot).

##### Retrospective versus momentary assessments

Participants will be asked to complete monthly assessments at irregular intervals for 6 months. Whenever an assessment is due (as per the sampling protocol), a notification will be displayed on a participant’s handset. There will be two types of notifications: one for the *Check Back* feature and one for the *Check In* feature of BrightSelf. The visual appearance of the notifications will depend on the operating system and on the model of the participant’s handset. The text of the notifications, however, will remain constant across participants for each type of notification.

Participants will be able to respond (and thus complete the corresponding assessments) or to dismiss the notifications. In addition, participants will be able to leave notifications unanswered. If participants do not complete an assessment in response to a notification, they will not receive reminders or follow-up notifications. In these instances, the non-response will be recorded in our database and will be coded as such for the purposes of our data analysis.

Outside assessment periods, participants will be able to use BrightSelf in any way they find convenient and there will be no restrictions on the number of assessments they can complete on a single day. However, we will be able to distinguish between assessments completed in response to a notification and those completed spontaneously. At baseline, participants will be randomly allocated to one of two types of assessment strategies:

##### Retrospective plus momentary assessments

In this experimental manipulation, participants will be asked to complete a combination of retrospective assessments and momentary assessments. A retrospective assessment will be defined as a single administration of the EPDS. A momentary assessment will be defined as the five momentary questions plus the two contextual questions.

Participants will be required to complete assessments for a total of 6 months, and each assessment period will consist of six consecutive days. The 6-month participation period will be calculated from the day on which the app is activated (ie, when participants enter their activation code and activate their account), and it will be divided into six intervals. All participants will receive the first notification 2 days after activating BrightSelf (ie, first assessment), while the use of the app is fresh within their minds and to give an idea of what to expect during the study. Subsequent assessment periods will be a random selection of six consecutive days within the 21–35 days following the end of the previous assessment period (in order to avoid 12 days of continuous assessments).

The assessment period will be structured as follows:Day 1: one retrospective assessment at any random time between 17:00 and 21:00Days 2–5: three momentary assessments per day, displayed at random times within each of the following intervals: 09:00–12:00, 13:00–16:00 and 17:00–20:00Day 6: one retrospective assessment at any random time between 17:00 and 21:00.

At the end of the 6-month period, participants will be sent a link via SMS or by e-mail to complete the non-validated, poststudy acceptance survey.

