## Methods and analysis

### Study design

We will assess the feasibility of using a bespoke mobile application, called BrightSelf, running on participants’ own smartphones to assess and monitor depression and mood during the antenatal period through a combination of retrospective assessments and ecological momentary assessments (EMA).

We will use a parallel, randomised controlled study design to assign our participants to one of two types of assessment strategies:Retrospective plus momentary assessment: requiring the completion of (1) the Edinburgh Postnatal Depression Scale (EPDS), (2) five momentary questions (assessing a participant’s mood, sleep, worry, enjoyment and energy levels), and (3) two contextual questions once a month for 6 monthsRetrospective assessment: requiring the completion of the EPDS once a month for 6 months.

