##### Retrospective assessments

In this experimental manipulation, participants will be asked to complete retrospective assessments only. A retrospective assessment will be defined as a single administration of the EPDS.

Participants will be required to complete assessments for a total of 6 months, and each assessment period will consist of 1 day. The 6-month participation period will be calculated from the day on which the app is activated (ie, when participants enter their activation code and activate their account), and it will be divided into six intervals. Again, all participants will receive the first notification 2 days after activating BrightSelf (ie, first assessment). Subsequent assessments will take place on a random day within the 21–35 days following the end of the previous assessment period (in order to avoid two consecutive EPDS assessments).

On each assessment day, participants will receive a notification to complete the EPDS at a random time between 17:00 and 21:00.

At the end of the 6-month period, participants will be sent a link via SMS or by e-mail to complete the non-validated, poststudy acceptance survey (see figure 3 for an illustration of both sampling protocols).

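### The gap between assessments is counted from the end of periods of unequal length, so the two arms run at different paces and the retrospective-only arm falls short of a monthly schedule

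*Protocol article*

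**What the plan says.** The protocol article describes the schedule in four places.

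- Study design gives the R arm as "requiring the completion of the EPDS once a month for 6 months" and puts the R+M arm on the same monthly, 6-month footing.
- Retrospective versus momentary assessments says of both arms: "Participants will be asked to complete monthly assessments at irregular intervals for 6 months".
- Retrospective plus momentary assessments sets the clock ("The 6-month participation period will be calculated from the day on which the app is activated"), the start ("All participants will receive the first notification 2 days after activating BrightSelf"), the block length ("each assessment period will consist of six consecutive days") and the rule for later blocks: "Subsequent assessment periods will be a random selection of six consecutive days within the 21–35 days following the end of the previous assessment period".
- Retrospective assessments has the same clock and start, a period of one day, and the rule "Subsequent assessments will take place on a random day within the 21–35 days following the end of the previous assessment period".

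Both arm descriptions say of the participation period that "it will be divided into six intervals". Neither ties the later assessments to those intervals. The text does not say whether the whole six-day block, or only its first day, must lie in the window.

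Under Outcomes, adherence counts women who complete every expected assessment, and timeliness uses the number of expected assessments as its first denominator. The acceptance survey goes out at the end of the 6 months in both arms.

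**The concern.** Both arms start on the same day, but each later period is timed from the end of the one before. A six-day block therefore adds its own length to every R+M cycle and a one-day assessment adds nothing to the R cycle. The arms drift apart by a fixed amount per cycle. This comes from the way the gap is anchored and has nothing to do with whether momentary questions are asked.

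Three things are at stake. Full adherence requires a response to the very last prompt, and that prompt comes later in R+M. The acceptance survey reaches the two arms at different distances from their last prompt. Women are also at different gestations at the same numbered period. Separately, the R rule does not produce the monthly schedule in six intervals that the article describes.

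**Working it through.** **Inputs.** From the article: first notification on day 2 (activation is day 0); gap of 21–35 days from the end of the previous period; period length 1 day (R) or 6 days (R+M); 6 months in six intervals. Assumed: every permitted day is equally likely, 6 months is 182 days, and there are six periods.

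**The plan's own target.** Six even intervals are 182 / 6 = 30.3 days each. Starting on day 2, the sixth period would begin on day 2 + 5 × 30.3 = 153.7, about day 154.

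**R arm.** Mean step = (21 + 35) / 2 = 28 days.
- Sixth assessment: mean day 2 + 5 × 28 = 142.
- Range: 2 + 5 × 21 = 107 to 2 + 5 × 35 = 177.
- SD: √(5 × (15² − 1) / 12) = 9.7 days.
- Shortfall against the even schedule: 153.7 − 142 = 11.7, about 12 days.

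**R+M arm, whole block inside the window.** The first block is days 2–7. The next start is 21–30 days after the previous end, so the next end is 26–35 days after it, mean 30.5.
- Sixth block ends on mean day 7 + 5 × 30.5 = 159.5 and starts on day 154.5.
- Latest possible end: 7 + 5 × 35 = 182, so all six blocks always fit.

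**R+M arm, only the start inside the window.** The next start is 21–35 days after the previous end, so the next end is 26–40 days after it, mean 33.
- Sixth block ends on mean day 7 + 5 × 33 = 172 and starts on day 167.
- From the exact distribution of the summed draws, the sixth block ends by day 182 with probability 0.857, so about 14% of women finish later (about 10% if 6 months is taken as 184 days).

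| | R | R+M, whole block | R+M, start only |
|---|---|---|---|
| Mean cycle (days) | 28 | 30.5 | 33 |
| Sixth period, mean days | 142 | 154.5–159.5 | 167–172 |
| Day 1 of sixth period, later than R | – | 12.5 | 25 |
| Last prompt, later than R | – | 17.5 | 30 |
| Mean days from last prompt to day 182 | 40 | 22.5 | 10 |

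Of the 17.5 days between last prompts, 5 × 2.5 = 12.5 come from the difference in pace. The other 5 are the length of the final block, which is part of the design.

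**Scale.** Expected assessments are 6 in R and 6 × (2 EPDS + 4 × 3 momentary) = 84 in R+M.

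**The case against.** Several stronger readings are tempting, and the article does not support them.

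- **That follow-up time differs by arm.** It does not. Participation is 6 months from activation in both arms, and dropout is defined on that period. Only the span covered by prompts differs.
- **That the number of assessments is random and differs by arm.** If prompts ran on to day 182, a seventh period would start for about 88% of R women and 36% of R+M women (whole-block reading). But no section says that prompts go beyond six. The monthly wording and the six intervals point to six, and Figure 3, which is not shown here, may settle it.
- **That neither arm fills the 6 months.** Six monthly assessments starting on day 2 leave about 182 − 154 = 28 days after the last one in any case. The R shortfall is about 12 days, not 40. On the whole-block reading the R+M arm is on schedule: 154.5 against about 154.
- **That EPDS scores will be compared between arms at the wrong gestation.** No comparison by sequence number is planned. Inferential statistics compares day 1 with day 6, which exists only in R+M, and otherwise names models that can use time directly.

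It is also fair to say that anchoring on the end of a block has a stated purpose, to prevent back-to-back blocks; that pacing could be seen as part of the two sampling protocols under comparison; and that the random draws already spread the sixth R assessment over 70 days.

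These points reduce the size of the problem but do not remove it. The unequal pace follows from the text on either reading of the window, the R rule still misses the monthly schedule, and back-to-back blocks can be avoided without an arm-specific pace.

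**Conclusion.** The point holds in limited form. The scheduling rules give mean cycles of 28 days in R and 30.5 in R+M (33 on the start-only reading). The misfit with monthly assessment in six intervals lies mainly in the R rule. On the start-only reading it also touches R+M, where about one woman in seven would finish the sixth block after day 182.

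The consequences are an arm difference of 17.5 days in the span needed for full adherence, 40 against 22.5 days from last prompt to acceptance survey, and 12.5 days of gestation at the sixth period. Beside 6 against 84 expected assessments and an all-or-nothing adherence criterion, these are unlikely to change how the adherence comparison is read. The point is worth correcting because the difference is unrelated to the intervention and easily avoided.

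The figures assume uniform draws, six periods and 182 days.

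**What to change.** Reconcile Study design, Retrospective versus momentary assessments and the two arm descriptions:

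1. Generate Day 1 of every period by the same rule and from the same reference point in both arms, either the previous Day 1 or the activation date. Keep a minimum gap so that blocks still cannot run together.
2. State that six periods are expected, and use that count to define expected assessments for adherence and timeliness.
3. State whether the whole six-day block, or only its first day, must lie in the window.
4. In the longitudinal models under Inferential statistics, use actual days since activation as the time variable.

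Before launch the cost is a small change to the notification generator and a few lines of protocol text. After launch the pace can no longer be equalised for women already scheduled, but items 2 and 4 can still be adopted at no material cost, and item 3 can be reported as it was implemented.

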##### Retrospective assessments

In this experimental manipulation, participants will be asked to complete retrospective assessments only. A retrospective assessment will be defined as a single administration of the EPDS.

Participants will be required to complete assessments for a total of 6 months, and each assessment period will consist of 1 day. The 6-month participation period will be calculated from the day on which the app is activated (ie, when participants enter their activation code and activate their account), and it will be divided into six intervals. Again, all participants will receive the first notification 2 days after activating BrightSelf (ie, first assessment). Subsequent assessments will take place on a random day within the 21–35 days following the end of the previous assessment period (in order to avoid two consecutive EPDS assessments).

On each assessment day, participants will receive a notification to complete the EPDS at a random time between 17:00 and 21:00.

At the end of the 6-month period, participants will be sent a link via SMS or by e-mail to complete the non-validated, poststudy acceptance survey (see figure 3 for an illustration of both sampling protocols).

**Figure 3 F3:**
[figure not shown]
Sampling protocols for the retrospective plus momentary assessments and for the retrospective assessments. EPDS, Edinburgh Postnatal Depression Scale.

##### Duty of care

Regardless of participants’ allocation, the central research team will be alerted if any of a series of prespecified conditions are met (table 2). These alerts will be colour-coded according to their severity level. In order to determine the severity level, we have chosen commonly used EPDS scoring thresholds (ie, 10–12 points for possible depression, and 13 points or more for probable depression). We acknowledge the limitations of this approach as the diagnostic accuracy of the EPDS can vary depending on the setting and the population in which it is administered.

**Table 2 T2:** Criteria for an alert to be sent to the research team

**Type of alert**	**Criteria**
Yellow (Mild)	Completing more than one EPDS assessment on the same day, with an overall EPDS score of 9 points or less and a score of 0 on question 10 of the EPDS
Orange (Moderate)	Overall EPDS score between 10 and 12 points, with a score of 0 on question 10 of the EPDS
Red (Severe)	Overall EPDS score of 13 points or more, and 1 or more points on question 10 of the EPDS, regardless of the overall EPDS score

EPDS, Edinburgh Postnatal Depression Scale.

Before starting the study, the central research team will agree on a list of designated contacts with the relevant clinical care teams. These contacts will include clinicians who are available during normal working hours, as well as those on duty outside working hours (including weekends and bank holidays). If a red or orange alert is generated, the study coordinator will contact the designated member of the clinical care team by phone and e-mail within 24 hours of receiving the alert. The clinical care team will then follow up these alerts directly with the participants.

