### Data analysis plan

#### Descriptive statistics

We will report the number of potential participants who were eligible and refused to take part in the study. Where possible, we will report the reasons for refusing to participate.

For each experimental group, we will report the following information:Demographic characteristics (as captured by the non-validated, sociodemographic survey)Proportion of participants answering Yes to any of the Whooley questions during the baseline assessmentProportion of participants scoring at each interval of the EPDS: between 0 and 9 points, between 10 and 12 points, and 13 points or above during the baseline assessmentProportion of participants scoring 1 or more points on question 10 of the EPDS during the baseline assessment.

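### The red-alert row of Table 2 joins its two triggers with *and* where the rest of the text points to *or*; taken literally, 48 of 112 score combinations fit no row

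*Protocol article*

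**What the plan says.** The Duty of care section sets three alert levels in Table 2.

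- **Yellow:** more than one EPDS on the same day, with a total of at most 9 and item 10 at 0.
- **Orange:** "Overall EPDS score between 10 and 12 points, with a score of 0 on question 10 of the EPDS".
- **Red:** "Overall EPDS score of 13 points or more, and 1 or more points on question 10 of the EPDS, regardless of the overall EPDS score".

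The text above the table bases severity on common EPDS cut-offs, including "13 points or more for probable depression", with no item 10 condition attached. The action follows the colour: "If a red or orange alert is generated, the study coordinator will contact the designated member of the clinical care team", with a 24-hour limit. No such contact is attached to yellow.

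The EPDS section adds that "special attention should be paid to item 10, as it deals with suicidal thoughts". The Descriptive statistics section tabulates a baseline total of 13 or above separately from the proportion "scoring 1 or more points on question 10 of the EPDS during the baseline assessment".

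**The concern.** The red row first demands a total of at least 13 together with a positive item 10, and then says that the total does not matter. Both cannot be true of one conjunctive rule. The yellow row of the same table uses *and* for conditions that must hold together, so a reader has some reason to read red the same way.

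On that reading two groups drop out of the table:

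- women with a total of 13 or more and item 10 at 0;
- women with any positive answer on suicidal thoughts and a total of 12 or less. Yellow and orange cannot catch them, because both require item 10 at 0.

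The article itself marks both groups as needing attention. The rule would also run backwards: a total of 12 with item 10 at 0 is orange and leads to contact, whereas a total of 20 with item 10 at 0, or a total of 12 with item 10 at 3, leads to none. Table 1 excludes women who have a current mood-disorder diagnosis, are under treatment, or have a history in the past 12 months. Participants therefore start without current treatment for depression, and the alert is the only study-initiated contact with clinicians that the article describes.

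**Working it through.** The article gives no count for the alert rule, so there is no stated figure to reproduce. The check is a full enumeration.

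**Inputs.** From the EPDS section: ten items, each scored 0 to 3, summed to a total. From Table 2: the three row definitions above.

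**Feasible pairs.** Let k be the item 10 score (0 to 3) and s the sum of the other nine items (0 to 9 × 3 = 27). The total is T = s + k, so for a given k, T runs from k to 27 + k. That gives 4 × 28 = 112 pairs (T, k).

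**Rows that are clear.** Yellow is counted on its score condition alone, ignoring the same-day requirement, which favours the protocol.

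- Yellow range (T ≤ 9, k = 0): T = 0 to 9, 10 pairs.
- Orange (T = 10 to 12, k = 0): 3 pairs.

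**Red read as *and* (T ≥ 13 and k ≥ 1).**

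| k | Range of T | Red | Orange | Yellow range | No row |
|---|---|---|---|---|---|
| 0 | 0–27 | 0 | 3 | 10 | 15 (T = 13–27) |
| 1 | 1–28 | 16 | 0 | 0 | 12 (T = 1–12) |
| 2 | 2–29 | 17 | 0 | 0 | 11 (T = 2–12) |
| 3 | 3–30 | 18 | 0 | 0 | 10 (T = 3–12) |
| All | | 51 | 3 | 10 | 48 |

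Check: 51 + 3 + 10 + 48 = 112. The 33 unmatched pairs with k ≥ 1 split into 3 × 3 = 9 with T = 10–12, and 9 + 8 + 7 = 24 with T ≤ 9. So 48 = 15 + 9 + 24.

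**Red read as *or* (T ≥ 13 or k ≥ 1).** All 3 × 28 = 84 pairs with k ≥ 1 are red, plus the 15 pairs with k = 0 and T = 13–27, giving 99. Then 99 + 3 + 10 = 112: no pair is unmatched and none meets two rows.

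**A woman who completes one EPDS that day.** Yellow cannot apply, so the 10 yellow-range pairs also raise no alert. The no-alert counts become 48 + 10 = 58 under *and*, and 0 + 10 = 10 under *or*. Those last 10 are low totals with item 10 at 0, where silence is evidently intended.

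**Which reading the article supports.** Four things point to *or*: the row's closing clause makes sense only for a stand-alone item 10 trigger; yellow and orange both require item 10 at 0, which leaves red as the only place for a positive item 10; the 13-point cut-off is stated without an item 10 condition; and item 10 is singled out for its content. Under *or*, the three rows also partition the score space exactly. The separate baseline categories in Descriptive statistics agree with this but are weaker evidence, since they do not concern alerts.

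**The case against.** The strongest reply is that nobody would apply the conjunctive reading. The closing clause defeats it, and *and* after a comma can list two triggers. The sentence introducing the table says the team is alerted when any one of several preset conditions is met, which is disjunctive language. The intended rule can be recovered from the same section without outside sources. The figure of 48 arises only under a reading that the context rejects, and it weights rare and common score patterns equally. Finally, "A complete description of BrightSelf is the aim of another publication", so the operational alert logic sits elsewhere and may well be right.

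Much of this stands. The intent is recoverable, the count is not a measure of harm, and the article gives no evidence of a coding error. Two parts do not remove the point. The introductory sentence most naturally refers to the rows of the table, so it does not settle the grammar inside the red row. And that the reader must infer the rule is itself the defect: this is the printed decision rule for clinical contact, and a programmer, tester or later trial should be able to apply it as written.

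The article also says participants are told that "if they feel they need immediate help at any point during the study they should contact their general practitioners". That supplements an alert, but it depends on the woman acting herself and does not replace one.

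**Conclusion.** The red row is wrong as written and should be corrected. Taken literally as a conjunction it leaves 48 of 112 score combinations in no row; read as *or*, it leaves none. The counts are exact given ten items scored 0 to 3, and they treat the yellow row as met on score alone. They describe combinations, not participants, and are not an estimate of risk. The possible harm is conditional: it arises only if the alert logic is programmed or checked from the literal wording, which the article neither shows nor rules out. Endpoints, sample size and analysis do not depend on this row.

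**What to change.** Reword the red criterion so that the triggers are separate: *EPDS total of at least 13, or a score of at least 1 on question 10 whatever the total*.

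Before enrolment, run the programmed alert logic on all 112 pairs. Expect red for 99 and orange for 3. For the 10 with a total of 0–9 and item 10 at 0, expect yellow only when more than one EPDS is completed on the same day, and otherwise no alert.

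The rewording changes one word of substance in one table row. The test is a routine software check, added as a precaution because the article does not show the programmed rule. Nothing else in the design or analysis changes.
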